# A prospective double-blinded randomised control trial comparing robotic arm-assisted functionally aligned total knee arthroplasty versus robotic arm-assisted mechanically aligned total knee arthroplasty

**DOI:** 10.1186/s13063-020-4123-8

**Published:** 2020-02-18

## Abstract

**Background:**

Total knee arthroplasty (TKA) with mechanical alignment (MA) aims to achieve neutral limb alignment in all patients, whereas TKA with functional alignment (FA) aims to restore native, patient-specific anatomy and knee kinematics by manipulating bone resections and fine-tuning implant positioning. The objective of this study is to determine the optimal alignment technique in TKA by comparing patient satisfaction, functional outcomes, implant survivorship, complications, and cost-effectiveness in MA TKA versus FA TKA. Robotic technology will be used to execute the planned implant positioning and limb alignment with high-levels of accuracy in all study patients.

**Methods and analysis:**

This prospective double-blinded randomised control trial will include 100 patients with symptomatic knee osteoarthritis undergoing primary robotic arm-assisted TKA. Following informed consent, patients will be randomised to MA TKA (the control group) or FA TKA (the investigation group) at a ratio of 1:1 using an online random number generator. Blinded observers will review patients at regular intervals for 2 years after surgery to record predefined study outcomes relating to postoperative rehabilitation, clinical progress, functional outcomes, accuracy of implant positioning and limb alignment, gait, implant stability, cost-effectiveness, and complications. A superiority study design will be used to evaluate whether FA TKA provides superior outcomes compared to MA TKA. Primary and secondary objectives will be used to quantify and draw inferences on differences in the efficacy of treatment between the two groups. Intention-to-treat and per-protocol population analysis will be undertaken. The following statistical methods will be employed to analyse the data: descriptive statistics, independent *t* test, paired *t* test, analysis of variance, Fisher exact test, chi-square test, and graphical displays. Ethical approval was obtained from the London-Surrey Research Ethics Committee, UK. The study is sponsored by University College London, UK.

**Discussion:**

This is the first study to describe the use of robotic technology to achieve FA TKA, and the only existing clinical trial comparing robotic MA TKA versus robotic FA TKA. The findings of this study will enable an improved understanding of the optimal alignment technique in TKA for achieving high-levels of patient satisfaction, improving functional outcomes, increasing implant survivorship, improving cost-effectiveness, and reducing complications.

**Registration:**

Clinical Trials.gov, NCT04092153. Registered on 17 September 2019.

## Background

Total knee arthroplasty (TKA) is an established and highly effective treatment for patients with symptomatic end-stage knee osteoarthritis. The procedure is performed in over 90,000 patients per year in the UK [1]. Middle- to long-term follow-up studies have shown good clinical outcomes following TKA [20, 22, 39], and the 10-year revision rate for cemented, unconstrained, fixed bearing TKA is 3% [1]. Despite these results, there is a higher incidence of patient dissatisfaction compared to total hip arthroplasty, with up to 20% of patients reporting dissatisfaction in an otherwise uncomplicated TKA [5, 9, 10, 35]. The exact aetiology of this is not clear but recent studies have shown one possible reason to be suboptimal limb alignment, which may adversely affect postoperative knee biomechanics and kinematic function [4, 7, 9–11, 35, 44]. Conceptually, an improved understanding and execution of the optimal alignment in TKA may help to increase patient satisfaction, improve functional outcomes and reduce long-term complications.

Total knee arthroplasty with mechanical alignment (MA) aims to achieve neutral alignment of the limb. This is achieved by placing implants perpendicular to the mechanical axis of the femur and tibia, and externally rotating the femoral component to obtain a rectangular, balanced flexion-extension gap, which also aids patella tracking [11]. Measured bone resections or gap balancing techniques with controlled periarticular soft tissue releases help to achieve balanced flexion-extension gaps and restore equal mediolateral soft tissue tension. The principle of neutral mechanical alignment is to distribute load evenly across the implants, which provides a mechanical advantage in flexion and limits asymmetrical bearing surface wear [44]. However, recent studies have shown that there are large variations in native knee anatomy with only 5–5.5% of the general population having natural neutral mechanical alignment [4, 6]. Therefore, in the large majority of patients undergoing MA TKA, the knee is forced into an unnatural position with resultant changes in knee biomechanics that alter the native femoral flexion axis, ligament tension, quadriceps function, patella tracking and overall knee kinematics [4, 6, 17, 18].

Total knee arthroplasty with functional alignment (FA) aims to restore joint line height, preserve native obliquity, and achieve balanced flexion-extension gaps with equal mediolateral soft tissue tension by manipulating bone resections and fine-tuning implant positioning. Conceptually, FA TKA reduces the need for intraoperative periarticular soft tissue releases while restoring the patient’s native pre-arthritic knee kinematics. This technique is a modification of TKA with kinematic alignment, in which bone resections and implant positioning are undertaken to restore the patient’s natural distal and femoral joint lines, tibial joint line and limb alignment. Patient-specific implants, computer navigation and three-dimensional printed cutting blocks have been used to help achieve kinematic alignment in TKA. Studies have demonstrated that TKA with kinematic alignment reproduces more natural knee kinematics including medial pivot movement and femoral rollback compared to MA TKA [14, 34, 15, 26, 29]. Preserving patient-specific alignment and knee kinematics in TKA with kinematic alignment may also decrease the risk of common peroneal nerve palsy, which is associated with forcing the limb into neutral alignment with extensive bone resections and periarticular releases in MA TKA [23, 25]. Early clinical and functional outcome studies have reported promising outcomes in TKA with kinematic alignment [14, 27, 28], but results of longer-term studies have yet to be published.

There is no uniform consensus on the optimal alignment technique for TKA [8, 12, 16, 19, 30, 33, 36–38, 41]. Some studies have shown improved clinical outcomes with TKA with kinematic alignment compared to MA TKA at short-term follow-up, while other systematic reviews and meta-analyses have shown no difference in outcomes between the two alignment techniques [14, 27, 28, 34, 44]. The main limitations of these existing studies are that different implant designs were used within each treatment group, manually positioned cutting blocks with poor reproducibility were used to achieve the planned limb alignment, intraoperative limb alignment was not assessed, and limited data on functional outcomes or implant survivorship were reported. It is possible to improve on these existing studies by assessing a more comprehensive range of validated clinical and functional outcome measures, blinding both patients and observers recording outcomes, and using radiosteriometric analysis (RSA) to assess implant micromotion for long-term implant survivorship [32, 42, 43]. Importantly, FA TKA offers an avenue for achieving patient-specific kinematics with balanced flexion-extension gaps and equal mediolateral soft tissue tension by manipulating bone resections and fine-tuning implant positioning, while limiting the need for periarticular soft tissue releases. Robotic technology also offers an avenue for executing the planned MA TKA or FA TKA with greater accuracy and reduced outliers. The findings of this study will enable an improved understanding of the optimal alignment technique in TKA for achieving high levels of patient satisfaction, improving functional outcomes, increasing implant survivorship, improving cost-effectiveness and reducing complications.

## Methods/design

### Objectives

The primary objective of this study is to compare the total Western Ontario and McMaster Universities Arthritis Index (WOMAC) score in MA TKA versus FA TKA at 2 years after surgery. As FA TKA enables improved restoration of native, patient-specific knee kinematics [15, 26, 29], the study hypothesis is that total WOMAC scores will be superior in patients undergoing FA TKA compared to MA TKA at 2 years follow-up.

The secondary objectives are to compare the following outcomes between the two treatment groups:
Accuracy of implant positioning and limb alignmentSurgical efficiencyPostoperative functional rehabilitationFunctional outcomesQuality of lifeImplant migrationGaitResource use and cost-effectivenessComplications

### Trial design

This study is a prospective, single-centre, double-blinded, randomised control trial. The study will be undertaken in the Department of Trauma and Orthopaedics, University College Hospital, London, UK. The study will include 100 patients randomly allocated to either MA TKA (the control group) or FA TKA (the investigation group). All patients will undergo robotic arm-assisted TKA to improve the accuracy of achieving the planned implant positioning and limb alignment. The study commenced patient recruitment in December 2018 and is expected to complete patient recruitment in December 2020. All patients will be followed up for 2 years after surgery and therefore the anticipated completion date for the study is December 2022. The study is sponsored by University College London, UK. The patient enrolment flowchart is presented in Fig. 1. The schedule of enrolment, interventions, and assessments for all study patients is shown in Fig. 2. This study followed the Standard Protocol Items: Recommendations for Interventional Trials (SPIRIT) (Additional file 1).

**Fig. 1 Fig1:**
[figure not shown]
Patient enrolment flow chart. CT computerised tomography, RSA radiosteriometric analysis, TKA total knee arthroplasty

**Fig. 2 Fig2:**
[figure not shown]
Schedule of enrolment, interventions, and assessments for all study patients*.* Legend: *CT* computerised tomography, *FA TKA* total knee arthroplasty with functional alignment, *MA TKA* total knee arthroplasty with mechanical alignment

### Eligibility criteria

The inclusion criteria for this study are as follows: 1) the participant has symptomatic knee osteoarthritis requiring primary TKA; 2) the participant is fit for surgical intervention following a review by the surgeon and anaesthetist; 3) the participant is aged between 18 and 80 years at the time of surgery; 4) the participant is able to give informed consent and agrees to comply with the postoperative review programme; and 5) the participant has sufficient mobility to attend follow-up clinics. The exclusion criteria for this study are as follows: 1) the participant is undergoing revision surgery or second-stage TKA; 2) the participant is not suitable for study implants (e.g. requires a constrained prosthesis); 3) the participant is immobile or has another neurological condition affecting musculoskeletal function; 4) the participant is already enrolled on another concurrent clinical trial; 5) the participant is unable or unwilling to sign the informed consent form specific to this study; and 6) the participant is unable to attend the study follow-up programme.

### Recruitment

Participants will be recruited from the orthopaedic outpatient clinic at University College Hospital, London, UK. All patients will be screened by the clinical team (orthopaedic consultant surgeon, clinical research fellow, and orthopaedic registrar) for study participation based on the predefined inclusion and exclusion criteria listed above. Patients that fulfil the eligibility criteria and express an interest in participating in the study will be provided with an Ethics Committee-approved patient information sheet. This provides details about the study, treatment, follow-up and contact details for further information. All members of the clinical team are familiar with the study and will address any preliminary questions about the study. Details of those patients expressing an interest to participate in the study will be recorded in the patient contact form and forwarded to the research physiotherapist. The research physiotherapist will telephone the patient 4 weeks after this consultation to discuss any further questions and confirm if the patient would like to participate in the study.

### Consent

Informed consent will be obtained by the chief investigator or principal investigator when the patient attends for the preoperative planning computerised tomography (CT) scan. This is 6 weeks after the outpatient consultation for agreement to TKA and 2 weeks before surgery. It is important to the data collection scheme that patients are able to follow commands and read and interpret questions via questionnaires. For those who cannot hear, read or understand English, an interpreter will be provided. The operating surgeon will use the preoperative CT scan to create a patient-specific computer-aided design model and create a surgical plan for executing both MA TKA and FA TKA in all study patients.

### Allocation

After informed consent has been obtained, the research physiotherapist will randomise the patient into one of the two groups using an online random number generator (www.random.org). A number from 1 to 100 will be randomly generated and will allocate a patient to one of the two arms of the study: 1–50 inclusive for the control group, 51–100 inclusive for the investigation group. The research physiotherapist will perform the randomisation procedure and store the designated treatment group for each patient on a password-encrypted file on the hospital computer. The operating surgeon will have this information communicated to him on the morning of surgery.

### Surgical intervention

In patients undergoing MA TKA, femoral and tibial bone implant positioning will be used to achieve neutral limb alignment. In the coronal plane, femoral implant positioning will be set at 5–7 valgus in relation to the anatomical axis of the femur. In the sagittal plane, femoral component positioning will be set at 0–5° of flexion to optimise implant positioning while preventing notching. In the axial plane, the femoral component will be aligned to the surgical transepicondylar axis, which is approximately 3° externally rotated to the posterior condylar axis [2, 3]. The size of the femoral implant will be selected using posterior referencing with the largest size that does not overhang the femur, notch the anterior femur, or overhang the mediolateral bone edges, and avoids overstuffing the patellofemoral joint. The femoral implant will be positioned at the centre of the mediolateral cortical bone edges. In the coronal plane, tibial implant position will be aligned to the tibial mechanical axis. In the sagittal plane, tibial implant position will be set to 0–3° of posterior tibial slope. In the axial plane, tibial implant will be positioned at 0–5° of external rotation to Akagi’s line [2, 3, 45]. Tibial implant size will be selected with the largest size that does not overhang the anteroposterior or mediolateral bone coverage. The implant will be positioned in the centre between the anteroposterior and mediolateral cortical bone edges.

In patients undergoing FA TKA, implants will be positioned to optimise soft tissue tension through achieving balanced flexion-extension gaps and equal mediolateral soft tissue tension by altering bone resections and implant positions rather than through soft tissue releases. This will be achieved when possible within strict alignment limits, and where not achievable because of the magnitude of a fixed deformity by balancing after bone cuts with limited soft tissue releases. The preoperative surgical plan will be used to fix a specific point on the tibia and the gaps balanced to restore the obliquity of the native joint line. In the coronal plane, femoral implant positioning will be modified from a starting point of 0° to the mechanical axis to balance the extension gap. In the sagittal plane, femoral component positioning will be set to optimise component sizing while avoiding notching by flexing up to 5°. In the axial plane, the femoral component will be aligned to the surgical transepicondylar axis and modified by up to 3° to balance the flexion gap. The size of the femoral implant will be selected using posterior referencing with the smallest size that does not overhang the femur, notch the anterior femur, or overhang mediolateral bone edges, and avoids overstuffing the patellofemoral joint. The femoral implant will be positioned at the centre of the mediolateral cortical bone edges, favouring a lateral position if necessary. In the coronal plane, tibial implant position will be aligned to the tibial mechanical axis and then modified to balance flexion and extension gaps by up to 3° of varus. Valgus tibial position will be avoided. In the sagittal plane, tibial implant position will be set to match the patient’s native posterior tibial slope, modified to balance the flexion gap if necessary. In the axial plane, the tibial implant will be positioned using Akagi’s line [2, 3, 45]. Tibial implant size will be selected with the largest size that does not overhang the anteroposterior and mediolateral bone coverage while achieving the correct rotation. The implant will be positioned in the centre between the anteroposterior and mediolateral cortical bone edges.

All operative procedures will be undertaken using the Mako robotic arm interactive orthopaedic system (Stryker Limited, Kalamazoo, MI, USA) under the direct supervision of one arthroplasty surgeon ([name]). The cemented Stryker Triathlon (Stryker Navigation, Kalamazoo, MI, USA) cruciate-retaining knee system with asymmetrical patellar resurfacing will be used in both groups. All bone resections, implant positioning and limb alignment will be within regulatory approval for the Triathlon cruciate-retaining knee system. Overall limb alignment, defined as the sum of the femoral and tibial coronal rotations, will range from 3° of varus to 3° of valgus.

### Outcomes

All study patients will undergo review by two blinded observers (one orthopaedic registrar and one clinical research fellow) at 2 weeks, 6 weeks, 6 months, 1 year and 2 years following surgery. During these follow-up times, predefined clinical, functional and radiological outcomes will be recorded by these observers using case report forms. The following outcomes will be recorded in all study patients:
Accuracy of implant positioning and limb alignment as assessed using CT scans of the knee joint performed postoperatively at 6 weeks.Operating time (minutes)Time to hospital discharge (hours)Analgesia requirements during inpatient admission and postoperatively at 6 weeks, 6 months, 1 year and 2 yearsPatient-reported outcome measures including Forgotten Joint Score (FJS), Oxford Knee Score (OKS), short-form health survey of 12 items (SF-12), Knee Injury and Osteoarthritis Outcome Score (KOOS), WOMAC, University of California at Los Angeles score and University College Hospital functional knee score preoperatively and postoperatively at 6 weeks, 6 months, 1 year and 2 yearsHealth-related quality of life as measured using the European Quality of Life questionnaire with five dimensions for adults (EQ-5D) preoperatively and postoperatively at 6 weeks, 6 months, 1 year and 2 yearsMobilisation distance (metres) and use of mobility aids during inpatient admission and postoperatively at 6 weeks, 6 months, 1 year and 2 yearsRange of movement (degrees) in knee joint during inpatient admission and postoperatively at 6 weeks, 6 months, 1 year and 2 yearsFemoral and tibial implant early migration as assessed using RSA performed postoperatively at 2 weeks, 6 weeks, 6 months, 1 year, and 2 yearsGait analysis performed postoperatively at 6 months and 1 year using an instrumented treadmill with force platesResource use and cost-effectiveness, including comparisons between the two treatment groups relating to operating time, theatre efficiency, equipment and sterilisation costs, analgesia requirements, inpatient rehabilitation, time to discharge, outpatient follow-up, additional imaging costs and need for further surgery.Complications

The FJS, University of California at Los Angeles knee score, WOMAC, OKS, KOOS, SF-12 and EQ-5D are validated tools for the clinical assessment of patients after knee arthroplasty [21, 24, 31]. In addition, the blinded observer will record the University College Hospital functional knee score to assess overall pain, function and mobility. All study patients will undergo gait analysis using an instrumented treadmill with force plates (Kistler Gaitway, Kistler Instrument Corporation, Amherst, NY, USA) on a level platform. Gait analysis will be performed at the patient’s self-selected comfortable speed and maximum speed without running. Vertical ground reaction forces and spatiotemporal data will be obtained from force plates built into the treadmill. RSA radiographs will be performed at regular postoperative follow-up intervals to quantify motion between the implant and host bone, which is highly predictive of long-term implant survival [32, 40].

### Blinding

All patients and clinical staff recording postoperative study outcomes will remain blinded to the treatment group. Study patients will be identifiable with a unique study number. Only the research physiotherapist will have the key to identify individual patients and their respective treatment arm. Any documents related to the study will be archived directly at the study site by the research physiotherapist within a secure filing cabinet in a locked research office. This office has swipe card access with onsite security and 24-h closed-circuit television surveillance. Patient data will be logged electronically using each patient’s unique identification number with computer software on an encrypted, password-protected research computer.

### Sample size

Using data from a previous study recording functional outcomes, the mean WOMAC score at 2 years using MA TKA was 26 (standard deviation 22.6) and using TKA with kinematic alignment was 15 (standard deviation 20.3) [14]. Using a two-tailed, two-sample *t* test with an effect size of 0.35, power of 90% with significance level of 5%, and accounting for an expected drop-out rate of 10% during the 2-year follow-up period, the study requires 100 patients to detect a minimal clinically important difference of 11 points in the total WOMAC score between the two treatment groups [13].

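### The sample-size inputs contradict each other, and under the stated two-sample t test they do not give 100 patients at 90% power

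*Protocol article*

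**What the plan says.** The Sample size section of the protocol article takes its figures from an earlier study: "the mean WOMAC score at 2 years using MA TKA was 26 (standard deviation 22.6") for mechanical alignment, and "using TKA with kinematic alignment was 15 (standard deviation 20.3") for kinematic alignment. It names the method ("Using a two-tailed, two-sample" t test) and the parameters: "effect size of 0.35, power of 90% with significance level of 5%, and accounting for an expected drop-out rate of 10" per cent over the 2-year follow-up. It concludes that "the study requires 100 patients to detect a minimal clinically important difference of 11 points in the total WOMAC score".

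The Abstract gives 1:1 allocation. The Objectives section makes total WOMAC at 2 years the primary comparison. The Statistical analysis section compares the groups on each patient's change from baseline. The article gives neither an SD of change nor a correlation between baseline and 2-year scores.

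**The concern.** The paragraph sets out a complete calculation: test, sidedness, alpha, power, means, SDs, target difference, drop-out and total. It can therefore be checked without any outside source. Two of its inputs, the effect size of 0.35 and the 11-point difference with its SDs, describe different targets, and neither leads to 100 patients under the named test.

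The claim concerns the primary endpoint of a superiority trial. Readers use the stated power to judge what a non-significant result means. If the real power for 11 points is well below 90%, such a result says less against an 11-point benefit than the protocol implies.

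**Working it through.** **Inputs (Sample size section, with 1:1 allocation from the Abstract).** Means 26 and 15; SDs 22.6 and 20.3; difference 11; stated effect size 0.35; two-sided alpha 0.05; power 90%; drop-out 10%; total 100. After drop-out, 100 × 0.9 = 90 evaluable, or 45 per arm.

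**Step 1: do the effect size and the 11 points agree?**
- Pooled SD = √((22.6² + 20.3²)/2) = 21.48.
- d = 11/21.48 = 0.512.
- Conversely, 0.35 × 21.48 = 7.5 points.

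They do not agree.

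**Step 2: try to reproduce 100.** The normal approximation is n per arm = 2(1.960 + 1.282)²/d². The noncentral t adds about one patient per arm.

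| Input | n per arm, normal | n per arm, t | Evaluable total | After /0.9 |
|---|---|---|---|---|
| 11 points, SD 21.48 (d = 0.512) | 81 | 82 | 164 | 183 (184 for equal arms) |
| 0.35 read as d | 172 | 173 | 346 | 385 (386 for equal arms) |

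Neither gives 100. Using one SD alone does not help: SD 22.6 gives 90 per arm (200 after drop-out) and SD 20.3 gives 73 per arm (163 after drop-out).

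**Step 3: power with 100 randomised.** The normal approximation is power ≈ Φ(d√(n/2) − 1.960). For d = 0.512 and n = 45, this is Φ(2.429 − 1.960) = Φ(0.469) = 68%. The noncentral-t values are:

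| Scenario | 45 per arm | 50 per arm (no drop-out) |
|---|---|---|
| 11 points, SD 21.48 | 67% | 72% |
| 11 points, SD 22.6 | 63% | 67% |
| 11 points, SD 20.3 | 72% | 77% |
| 0.35 read as d | 38% | 41% |
| 0.35 read as Cohen's f (d = 0.70) | 91% | 93% |

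For two equal groups d = 2f. So f = 0.35 means 0.70 × 21.48 = 15.0 points, whereas 11 points means f = 0.512/2 = 0.26.

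**Step 4: what 45 per arm can detect with 90% power.** The required d is 0.691. At SD 21.48 that is 14.8 points. For 11 points, the SD would have to be 11/0.691 = 15.9.

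**Step 5: the contrast in the Statistical analysis section.** The SD of change is not given. Assume equal SDs of 21.48 at baseline and 2 years, with correlation r. Then SD of change = 21.48 × √(2(1 − r)). At 45 per arm and 11 points:

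| r | SD of change | Power |
|---|---|---|
| 0 | 30.4 | 40% |
| 0.5 | 21.5 | 67% |
| 0.7 | 16.6 | 87% |

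For 90% power the SD of change must be 15.9, so 1 − r = ½(15.9/21.48)² ≈ 0.27 and r ≈ 0.73.

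**The case against.** Three arguments favour the plan.

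**The planned analysis is not a comparison of raw 2-year scores.** This stands, and it limits the point. A reader might infer that the design has 67% power and would miss a true 11-point benefit about one time in three. The documents do not support that, because 67% belongs to the calculation as written. For change from baseline, power may be lower or higher, and reaches 90% if the correlation is about 0.73 or more. This does not rescue the stated 90%: the Sample size section works from 2-year scores and invokes no correlation, and below 0.5 change scores lose power.

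**0.35 might be Cohen's f.** On that reading 44 per arm suffice, 88 evaluable and 98 after drop-out, which is close to 100. But f is not the usual effect measure for the named t test, and 0.35 would then mean about 15 points, against a stated target of 11. It also means that 38% cannot be presented as the trial's power, since it holds only if 0.35 is d. The article does not say how 100 was obtained, and the finding does not depend on knowing.

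**The 11 points are cited as a minimal clinically important difference.** A reader might infer from 26 − 15 = 11 that the earlier study's observed difference was simply relabelled. The equality is a fact, but the article cites a separate source for the label. That source is not at hand, so no error is established.

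That a journal article condenses its protocol is no defence here: nothing is said to be missing, and the figures that are printed conflict.

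**Conclusion.** The paragraph is wrong as written. Under its own two-tailed two-sample t test, 11 points with its own SDs is d = 0.51, not 0.35, and needs about 183 to 184 patients with drop-out rather than 100. The shortfall in power on 2-year scores is from 90% to about 67%, or 72% with no drop-out. These figures rest only on the stated inputs, equal arms and the t-test model.

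The power of the planned change-from-baseline comparison cannot be fixed from the article. The range of 40% to 87% for correlations of 0 to 0.7 assumes equal SDs at the two time points and 45 evaluable patients per arm. The 90% claim could be true of that contrast, but only under a correlation that the article neither states nor uses.

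**What to change.** Rewrite the Sample size paragraph as follows.

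1. Remove or correct the effect size of 0.35 and the power of 90%. If an effect size is kept, name its type and make it agree with the target difference and SDs.
2. State that 100 randomised, with 45 evaluable per arm, gives about 67% power for 11 points on 2-year WOMAC scores at SD 21.5, or 90% power for about 15 points.
3. Add the power for change from baseline under a stated and justified correlation, showing the range (for example 40%, 67% and 87% at 0, 0.5 and 0.7 with equal SDs).
4. Note that 11 points equals the difference in the earlier study, and keep the clinical-importance label only if the cited source supports it.

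This is a change of wording. It needs no extra patients or visits; the only downside is a less favourable stated power. Whether to revisit the sample size is a separate decision for the sponsor, and is better taken from the corrected figures.
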